### Safety evaluation

2.10

All participants will undergo a safety evaluation before and after treatment. Adverse events (e.g., localized skin redness, swelling, itching) that occur during treatment will be recorded. In case of an adverse event, the cause will be determined, its correlation with AA treatment will be assessed, and symptomatic treatment will be provided. In addition, all participants will undergo professional depression assessment, and depressive symptoms will be recorded on the Case Report Form (CRF). If severe depression is detected, the trial will be terminated, and further treatment will be provided.

Safety will be evaluated according to the following adverse reaction grading system: Grade 1: Safe, no adverse reactions; Grade 2: Generally safe, mild adverse reactions that do not require treatment and allow continuation of therapy; Grade 3: Safety concerns, moderate adverse reactions, treatable but continuing therapy allowed; Grade 4: Trial termination due to adverse reactions.

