**Methods:**

This study is a single-center, double-blind, randomized controlled trial conducted in Nanjing, China. Participants are students from junior and senior high schools in Nanjing. A multi-stage stratified cluster sampling method is used to recruit students from 7th and 8th grades (junior high) and 10th and 11th grades (senior high). Baseline data will be collected using the Chinese version of the Pittsburgh Sleep Quality Index (PSQI), Beck Depression Inventory (BDI), Adolescent Sleep Hygiene Scale (ASHS), Children’s Depression Inventory (CDI), Adolescent Self-rating Life Events Checklist (ASLEC) and Adolescent Sleep-Wake Scale (ASWS), and insomnia patients will be identified. Adolescents who met the inclusion and exclusion criteria and whose guardians signed informed consent forms will be enrolled in the study. They will be randomly assigned to one of three groups: AA group, sham auricular acupressure (SAA) group, and control group. The treatment lasted for 8 weeks, with follow-up assessments at 3 and 6 months post-treatment. The primary outcome measures are PSQI and BDI scores, while secondary outcome measures included ASHS, CDI, ASLEC, and ASWS scores.

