#### Handling of dropouts

2.2.3

(1) Criteria for dropout

Patients who have provided informed consent, been screened and randomized for the trial, but for any reason do not complete the treatment and observation period as outlined in the study protocol will be considered dropouts.

(2) Handling of dropout cases

1) After a patient drops out, the researcher should contact the patient via home visits, scheduled follow-ups, phone calls, or letters to inquire about the reason for dropout, record recent sleep patterns, and complete any assessments that can be performed.

2) For patients who drop out due to allergies, adverse reactions, or treatment ineffectiveness, appropriate treatment measures should be taken according to their condition.

3) All dropout cases should be properly documented, both for archival purposes and for the required analysis in statistical evaluation. No additional patients will be recruited to replace dropouts.

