#### Trial termination

2.2.4

(1) If a serious adverse event occurs, or the researcher determines the trial should be stopped for this reason.(2) If the patient’s condition worsens, or if other issues arise during the trial that affect observation, the researcher may decide to stop the trial.(3) If significant protocol deviations occur during the implementation of the clinical trial, such as poor adherence to the protocol, making efficacy evaluation difficult, the trial may be stopped.(4) If the participant expresses unwillingness to continue with the trial and requests to withdraw.

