#### AA group

2.7.2

In the AA group, AA will be applied in addition to sleep hygiene education. Points: Shenmen (TF4, located in the triangular fossa, above the division of the ear lobe), Subcortex (AT4, on the inner side of the ear), Endocrine (CO18, anterior lower part of the ear canal), Liver (CO12, behind the lower part of the ear), Heart (CO15, central part of the ear), Kidney (CO10, below the upper and lower branches of the ear lobe) (**Figure 3**). These points will be carefully located according to the guidelines in the “Illustrated Ear Acupuncture” by Shanghai Science and Technology Publishing House. After evaluation, the most sensitive areas will be treated with ear acupressure beans. Each session will treat one ear, with changes to the other ear every 3 days. Patients will be instructed to press the acupressure beans 3–5 times per day, 1–2 minutes per session. The treatment will last for 8 weeks, followed by follow-ups at 3 months and 6 months.

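### Section 2.10 states adverse-event recording only for the 8-week treatment period, so serious events in the 6 months of follow-up have no stated recording

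*Protocol article*

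**What the plan says.** All references are to the protocol article.

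- **Recording period (2.10 Safety evaluation).** "Adverse events (e.g., localized skin redness, swelling, itching) that occur during treatment will be recorded". The skin signs are introduced as examples. The text goes on to adverse events in general: "In case of an adverse event, the cause will be determined, its correlation with AA treatment will be assessed".
- **Safety evaluation (2.10).** "All participants will undergo a safety evaluation before and after treatment". The later of these two evaluations is not dated.
- **Depression (2.10).** As a separate provision, "all participants will undergo professional depression assessment, and depressive symptoms will be recorded on the Case Report Form (CRF". No timing is given. Severe depression leads to termination and further treatment.
- **Durations.** Section 2.7.2 says "The treatment will last for 8 weeks, followed by follow-ups at 3 months and 6 months". The abstract fixes where the months are counted from: "The treatment lasted for 8 weeks, with follow-up assessments at 3 and 6 months post-treatment". The introduction also counts them from the end of treatment.
- **Stopping (2.2.4 Trial termination).** The first ground reads "If a serious adverse event occurs, or the researcher determines the trial should be stopped for this reason". It carries no time limit.
- **Dropouts (2.2.3).** After a dropout, "the researcher should contact the patient via home visits, scheduled follow-ups, phone calls, or letters to inquire about the reason for dropout". Recent sleep is recorded too, along with any assessments that can still be done.
- **Scales (2.7.1).** Regular follow-up uses the BDI and CDI among other scales, and signs of depression lead to treatment. This stands under the control group, but sleep hygiene education is given in all three arms.

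**The concern.** The article names one period for recording adverse events, and that period ends when treatment ends. Most of the observation time comes afterwards. A reader at a study site who finds a single stated period will probably take it as the rule.

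The participants are minors with insomnia. The introduction ties undiagnosed or untreated depression to suicide risk, and the trial aims at a method that can be called safe. If a pupil is admitted to hospital in month 4, the visible text gives that event no place in the trial record. The serious-event ground in 2.2.4 would then depend on the event surfacing by another route, such as the depression assessment, a scale or a dropout contact. A safety comparison of the arms over the whole study would rest on incomplete recording of serious events.

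**Working it through.** The article gives no figure to reproduce. The check has two parts: which provisions apply after week 8, and how much time lies there.

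**1. Provisions that could reach a serious event after week 8**

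| Provision | Reaches follow-up? | Records a serious event as such? |
|---|---|---|
| Adverse-event sentence, 2.10 | Not stated; names the treatment period | Yes, within that period |
| Safety evaluation, 2.10 | Later one undated; paired with the baseline one, it reads most naturally as end of treatment | Not stated for months 3 and 6 |
| Professional depression assessment, 2.10 | Not confined to treatment | Records depressive symptoms; timing and look-back not stated |
| BDI and CDI at follow-up, 2.7.1 and 2.8 | Yes | Scale scores, not event records |
| Dropout contact, 2.2.3 | Possibly | Asks the reason for dropout and recent sleep; does not cover pupils who stay in |
| Stopping ground, 2.2.4 | No time limit | A ground for action, not a recording provision |

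None of these states that serious events will be recorded between the end of treatment and month 6. Several of them could bring a psychiatric event to light.

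**2. Calendar time for one participant**

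Inputs: 8 weeks of treatment; 6 months of follow-up, converted to 26 weeks (an assumption).

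- Total: 8 + 26 = 34 weeks
- Within the stated period: 8/34 = 23.5%
- After it: 26/34 = 76.5%

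**3. Person-time across the trial**

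Inputs from section 2.3: 65 per arm, so 3 × 65 = 195 randomised; 52 per arm after the planned 20% dropout, so 3 × 52 = 156. Assumptions: 6 months = 183 days; in the 156 case, all dropout falls at the end of treatment.

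- Within the stated period: 195 × 56 = 10,920 person-days
- After it, all followed: 195 × 183 = 35,685; share 35,685/(10,920 + 35,685) = 35,685/46,605 = 76.6%
- After it, 156 followed: 156 × 183 = 28,548; share 28,548/(10,920 + 28,548) = 28,548/39,468 = 72.3%

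**4. Sensitivity: 6 months counted from randomisation**

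Section 2.7.2 read alone would allow this. It leaves 183 − 56 = 127 days after week 8.

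- All followed: 195 × 127 = 24,765; 24,765/35,685 = 69.4%
- 156 followed: 156 × 127 = 19,812; 19,812/(10,920 + 19,812) = 19,812/30,732 = 64.5%

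The abstract and introduction both count from the end of treatment, so 72% to 77% is the main range.

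**The case against.** The strongest reply is that this is a condensed journal article. Serious-event windows, visit questions and listings usually stand in the full protocol and CRF, and the schedule figure cannot be seen. This holds against any charge that detail is missing. It does not remove the point, because the article does state a recording period, and that period is shorter than its own serious-event stopping ground needs.

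The intervention is also a non-invasive ear patch, and recording local reactions during treatment only is sensible. That stands, and the fix leaves it alone.

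A reader might infer four stronger things that the document does not support:

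- **That 2.10 forbids later recording.** It says events during treatment will be recorded. It does not say that others will not be, and section 2.12 asks for timely and complete case notes.
- **That emerging depression goes unrecorded in follow-up.** It does not. The professional assessment, the CRF entry, the BDI and CDI, and the rule on severe depression all apply without being tied to the treatment period.
- **That 2.10 and 2.2.4 contradict each other.** An undated stopping ground can stand beside a recording sentence for the treatment period. Parts of 2.2.4, such as a participant's request to withdraw, also read as grounds for one participant to leave rather than for ending the whole trial. The two provisions are poorly matched, but they do not conflict.
- **That about three quarters of serious events would be missed.** The share is calendar time, much of it also covered by the depression provisions. The document gives no event rate, and none is assumed here.

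**Conclusion.** The point holds in a narrow form. The only adverse-event recording period that the article states is the 8 weeks of treatment. Serious events as such, after week 8 and up to 6 months post-treatment, have no stated recording, although a serious event is a stopping ground at any time. Depressive symptoms lie outside the gap.

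The size is about 26 of 34 weeks for a participant who completes the study. It measures the length of the period without stated recording and nothing more. The conclusion rests on the wording of 2.10, not on what the missing figure may contain; if a fuller document already sets a window to month 6, only the article's sentence needs aligning. Sample size, error rates and efficacy results are unaffected. Severity is low: this is a cheap improvement to safety recording in minors.

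**What to change.** Add to section 2.10, in substance: serious adverse events, including psychiatric admission and self-harm that comes to attention, will be recorded from randomisation to the 6-month follow-up; one neutral open question about any serious health event since the last contact will be asked at the 3- and 6-month visits and at dropout contacts; events will be listed descriptively by arm. Local skin reactions may stay limited to the treatment period.

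Two safeguards belong with it. The question should not mention the ear tape, so that evaluators stay blinded. Any direct enquiry about self-harm should stay within the professional depression assessment and its route to care, because section 2.11 has parents or guardians helping to complete and verify questionnaires.

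The cost is one question at two visits already planned and at contacts already required. No visit or test is added. The downside is slightly more CRF work and possibly a minor ethics amendment.

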#### Missing data handling and dropout analysis

2.9.3

Missing Data: Multiple imputation will be used to address missing data, leveraging intervariable correlations to generate plausible values and enhance result accuracy.

Dropout Analysis: The primary analysis will follow the per-protocol approach, including only subjects who adhered strictly to the study protocol. As a supplementary strategy, intention-to-treat (ITT) analysis will include all randomized participants regardless of protocol deviations or dropout status, preserving randomization integrity and minimizing selection bias. Additionally, baseline characteristics (e.g., age, sex, initial depression scores) of dropouts versus completers will be compared using chi-square or t-tests to assess systematic bias. Significant differences will prompt covariate adjustment in regression models.

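### With per-protocol as the primary analysis, participants stopped for severe depression can fall outside the primary BDI comparison

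*Protocol article*

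**What the plan says.** All references are to the protocol article.

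- **Outcome.** The abstract and section 2.8.1 list PSQI and BDI scores as the primary outcomes. Preventing depression is a stated aim of the study.
- **Stopping, section 2.10.** Every participant has a professional depression assessment. Then: "If severe depression is detected, the trial will be terminated, and further treatment will be provided".
- **Stopping, section 2.2.4.** There is a second, related route. If the patient's "condition worsens, or if other issues arise during the trial that affect observation, the researcher may decide to stop the trial". The same list, under the heading Trial termination, ends with "If the participant expresses unwillingness to continue with the trial and requests to withdraw".
- **Dropout, section 2.2.3.** Randomised patients who "for any reason do not complete the treatment and observation period as outlined in the study protocol will be considered dropouts". After dropout the researcher should make contact and "complete any assessments that can be performed".
- **Analysis set, section 2.9.3.** "The primary analysis will follow the per-protocol approach, including only subjects who adhered strictly to the study protocol". Then: "As a supplementary strategy, intention-to-treat (ITT) analysis will include all randomized participants regardless of protocol deviations or dropout status".
- **Missing data.** Section 2.9.3 plans multiple imputation and a baseline comparison of dropouts with completers. Section 2.9.2 plans mixed-effects models where many values are missing.

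**The concern.** The trial looks for differences between groups in depression scores. Its primary analysis is restricted by something that happens after randomisation, and one route out of that analysis is becoming severely depressed. Participants at the bad end of a primary outcome can therefore be missing from the analysis meant to compare that outcome.

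Two things are at stake. First, mean BDI within each arm would look better than it was. Second, the groups compared would no longer be the groups randomised. If auricular acupressure (AA) does reduce depression, fewer AA participants than controls would be removed, and part of the benefit would disappear from the primary result. Section 2.9.3 itself credits ITT with protecting the randomisation and limiting selection bias, yet gives it the supporting role.

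**Working it through.** No figure in the protocol is at issue. The check has two parts: whether the text leads where the concern says, and how large the effect could be.

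**Part 1: the chain in the text**

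1. Does termination in section 2.10 mean the participant or the whole trial? Section 2.2.4 puts a participant's own withdrawal under Trial termination, and section 2.10 goes on to offer treatment. The participant-level reading is the sensible one.
2. Is that participant a dropout? If treatment or observation is left incomplete, yes: section 2.2.3 covers non-completion whatever the reason.
3. Is a dropout outside the primary set? Section 2.9.3 limits the set to strict adherers and contrasts it with an ITT set that ignores dropout status. The natural inference is that dropouts are outside. No sentence says so outright.
4. Does anything bring them back? Multiple imputation and mixed models fill in or accommodate missing values, but neither is said to return excluded participants to the per-protocol set. The dropout comparison looks at baseline traits, whereas removal here depends on what happened later.

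**Part 2: size, AA against control**

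Inputs, all assumed because the protocol gives no BDI mean, SD or severity cut-off: normal BDI scores, SD 10, true means m = 14 (control) and m = 10 (AA), true difference 4.0. A fraction d of participants above cut-off T is removed, with the same d in both arms. The 65 per arm comes from section 2.3.

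Formulas, with a = (T − m)/10:

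- share above T: P = 1 − Φ(a)
- their mean: U = m + 10·φ(a)/P
- share removed: r = d·P
- mean of those who remain: (m − r·U)/(1 − r)

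At T = 29 and d = 1:

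- Control: a = 1.5, P = 0.0668, U = 33.39. Remaining mean = (14 − 0.0668 × 33.39)/0.9332 = 12.61. Removed: 65 × 0.0668 = 4.3 participants.
- AA: a = 1.9, P = 0.0287, U = 32.85. Remaining mean = (10 − 0.0287 × 32.85)/0.9713 = 9.32. Removed: 65 × 0.0287 = 1.9 participants.
- Difference: 12.61 − 9.32 = 3.29 instead of 4.0.

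| Cut-off T | All removed (d = 1) | Half removed (d = 0.5) |
|---|---|---|
| 25 | 2.87 | 3.50 |
| 29 | 3.29 | 3.66 |
| 33 | 3.61 | 3.81 |

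The d = 1 column is the largest shrinkage under equal removal in this model. It also treats the stop as if it were triggered by the BDI score itself. If the trigger is instead a clinical severity score with the same means and SD, correlated ρ with BDI within arms, the loss is multiplied by ρ: difference = 4.0 − ρ × (4.0 − value at d = 1). For ρ = 0.6, also an assumption, this gives 4.0 − 0.6 × 1.13 = 3.32, 4.0 − 0.6 × 0.71 = 3.57 and 4.0 − 0.6 × 0.39 = 3.77.

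**The case against.** **A mandated stop could count as adherence.** A participant stopped because section 2.10 requires it has arguably followed the protocol and could stay in the per-protocol set. The article does not exclude this reading. It does not state it either, and the dropout definition makes no exception for mandated stops. This is why the point is that such participants can be left out, not that they certainly will be.

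**Much of the data may survive.** Section 2.10 places the safety evaluation before and after treatment. A case found at week 8 may already have a post-treatment BDI, so that only the 3- and 6-month visits are at risk. Section 2.2.3 also asks for whatever assessments remain feasible. Both points stand and make the loss partial.

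**The ITT result will be reported alongside.** True, and it limits the harm. The headline result would still be the selected one.

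**The size is modest.** With SD 10 and 65 per arm, the standard error of the difference is 10 × √(2/65) = 1.75, so a shift from 4.0 to 3.3 is well within sampling error. That is fair. But it is a systematic shift that need not occur.

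Three stronger readings are tempting, and the document does not support them:

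- *Selection on the BDI score itself.* Section 2.10 ties the stop to severe depression alongside a professional assessment and names no BDI value. The selection is related to the outcome but not defined by it.
- *A bias favouring AA through closer watching.* In the AA arm, "Each session will treat one ear, with changes to the other ear every 3 days", and staff talk to participants at each replacement. However, that contact is described as being about pressing and bead placement. Section 2.7.1 gives controls regular follow-up with BDI and CDI, and section 2.10 assesses all participants for depression. The text gives no basis for unequal detection, and so none for an exaggerated or spurious benefit by that route.
- *One severe case ends the whole trial.* The wording allows this, but section 2.2.4 shows that the heading covers individual withdrawal.

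**Conclusion.** The concern holds in a limited form. The choice of per-protocol as primary is stated in section 2.9.3; it is not a detail left to an analysis plan. Combined with sections 2.10 and 2.2.3, it allows some of the most severe depression outcomes to drop out of the primary BDI analysis. Mean BDI within arms would then be understated, and the between-arm comparison may be biased.

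Neither the amount nor the direction can be fixed from the document. In the illustration, with removal at the same rate in both arms, the effect is attenuation: a true 4.0 points becomes no less than 2.9, 3.3 or 3.6 at cut-offs 25, 29 and 33, and stays closer to 4.0 if removal is incomplete or the trigger tracks BDI imperfectly. This rests on the assumed means, SD and cut-offs, on the participant-level reading of termination, and on dropouts being outside the per-protocol set. It should be fixed, with medium confidence: it affects a primary outcome, but the loss is partial and a full ITT analysis is already planned.

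**What to change.** 1. **Section 2.9.3:** make ITT the primary analysis, covering all randomised participants with the multiple imputation or mixed-effects model already planned. Keep per-protocol as the supplementary analysis.
2. **Section 2.10:** state that severe depression stops the study intervention for that participant and triggers treatment, while scheduled PSQI and BDI assessments continue to 6 months where the participant and guardian agree. This is in line with section 2.2.3, which already asks for feasible assessments after dropout.

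The clinical response to severe depression does not change. The cost is mostly rewording, plus a little extra follow-up effort for the few participants concerned. The primary estimate may be more conservative than a per-protocol one.

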#### Inclusion criteria

2.2.1

(1) The diagnosis met ICSD-3 criteria, characterized by difficulty initiating sleep (>20 minutes), difficulty maintaining sleep, or early morning awakening despite adequate sleep opportunity, accompanied by daytime functional impairment. These symptoms occurred at least three times per week and persisted for more than three months.(2) Age between 13–18 years;(3) PSQI score > 7;(4) No psychiatric medication treatment;(5) No communication or cognitive impairments;(6) Signed informed consent.

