#### Exclusion criteria

2.2.2

(1) Sleep disorders caused by organic diseases such as epilepsy, stroke, etc.;(2) Sleep disorders caused by schizophrenia or other severe psychiatric disorders;(3) Diagnoses of other sleep disorders, such as obstructive sleep apnea, REM sleep behavior disorder, or restless legs syndrome;(4) Received AA therapy for insomnia in the past month;(5) Alcohol and/or other drug abuse or dependence.

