### Randomization

2.5

After screening based on the inclusion and exclusion criteria, eligible adolescent insomnia patients will be randomly assigned in a 1:1:1 ratio to the AA group, SAA group, or control group. The randomization sequence will be generated by researchers who are not involved in the trial implementation or statistical analysis using SPSS 25.0 software. The sequence will be hidden using the envelope method, and each envelope will contain the randomization order for patient allocation. A designated person will be responsible for patient inclusion, and patients will receive the corresponding envelope in the order of enrollment.

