#### Control group

2.7.1

Sleep hygiene education: Actively communicate with the patient to understand the causes of insomnia, provide targeted guidance and explanations to alleviate negative emotions, and provide a sleep education manual. This includes informing patients about the importance of sleep, guiding them to create a good sleep environment, changing poor sleep habits, and engaging in regular physical exercise. The recommended exercise regimen consists of running (moderate-intensity aerobic activity) with a frequency of three sessions per week (24). Follow-up will be conducted regularly using ASHS, PSQI, ASWS, CDI, and BDI scales to assess sleep and psychological health. If the patient shows signs of depression, appropriate treatment will be provided.

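### Severe depression ends participation under 2.10 but is not an exclusion in its own right, so a pupil who already meets the stop rule can be randomised

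*Protocol article*

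**What the plan says.** **Stop rule.** Section 2.10 (Safety evaluation) gives every participant a professional depression assessment and states: "If severe depression is detected, the trial will be terminated, and further treatment will be provided". It gives no scale, cut-off or time point for that assessment. The same section says "All participants will undergo a safety evaluation before and after treatment".

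**Entry criteria.** Two of the listed criteria come near to severe depression. Inclusion criterion 4 (2.2.1) reads "No psychiatric medication treatment". Exclusion criterion 2 (2.2.2) reads "Sleep disorders caused by schizophrenia or other severe psychiatric disorders". No criterion names depression, and the only score used for entry is PSQI above 7.

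**Allocation.** Section 2.5 says: "After screening based on the inclusion and exclusion criteria, eligible adolescent insomnia patients will be randomly assigned in a 1:1:1 ratio".

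**Information at hand before that.** The abstract (Methods) says "Baseline data will be collected using the Chinese version of the Pittsburgh Sleep Quality Index (PSQI), Beck Depression Inventory (BDI" and goes on to list the CDI among other scales. It describes this before enrolment and random assignment.

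**Care during the trial.** Section 2.7.1 promises: "If the patient shows signs of depression, appropriate treatment will be provided". The other two arms receive their intervention on top of the same sleep hygiene education.

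**After a stop.** Under 2.2.3 a randomised patient who does not complete treatment and observation, for whatever reason, is a dropout and is not replaced. Section 2.9.3 makes the per-protocol analysis primary and ITT supplementary.

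**The concern.** The entry rules and the stop rule do not fit together. A condition that ends participation when found should normally keep a person out when it is present at screening. Here it does so only through two indirect filters, medication and causal attribution.

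At stake is an avoidable allocation. A minor could be randomised, stopped under the protocol's own rule, recorded as a dropout, not replaced, and probably lost from the primary analysis set. The trial also asks whether depression can be prevented, and a pupil who is already severely depressed cannot contribute to that question as intended.

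**Working it through.** **Step 1. Can one pupil satisfy both rules?** Take a pupil aged 13–18 with ICSD-3 insomnia, PSQI above 7, consent, and current severe depression without medication.

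| Rule | Effect on this pupil |
|---|---|
| Inclusion 4, no psychiatric medication | Passes, because untreated |
| Exclusion 2, sleep disorder caused by a severe psychiatric disorder | Excluded only if the insomnia is attributed to the depression |
| Other criteria in 2.2.1 and 2.2.2 | None refers to depression, BDI or CDI |
| 2.5, randomisation on the listed criteria | Randomised if the insomnia is not so attributed |
| 2.10, stop rule | Met once the depression is detected |

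The filters are real but incomplete. The Introduction says that most adolescent depression goes undiagnosed or untreated, which weakens the medication filter. It also describes insomnia as more often preceding depression than following it. An assessor who holds that view could decline to attribute the insomnia to the depression.

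**Step 2. Whose trial is terminated?** Section 2.2.4, headed Trial termination, includes "If the participant expresses unwillingness to continue with the trial and requests to withdraw". That is an individual event, so reading 2.10 as ending one pupil's participation is reasonable. It remains an inference.

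**Step 3. The plan's own numbers (2.3).** 52 / (1 − 0.20) = 65 per arm; 3 × 65 = 195; 195 / 0.20 = 975. All three reproduce. The planned dropout allowance is 65 − 52 = 13 per arm.

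**Step 4. Size under assumed rates.** The documents give no rate r for this group, so r is an assumption.

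- Expected number: 195 × r overall, 65 × r per arm.
- Chance of at least one, assuming independence: 1 − (1 − r)^195.
- Evaluable per arm if these losses come on top of 20% dropout: 65 × (1 − r) × 0.8.
- Power: two-sample t-test, d = 0.8, two-sided α = 0.05.

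| r | Of 195 | Per arm | At least one | Evaluable per arm | Power |
|---|---|---|---|---|---|
| 0 | 0 | 0 | – | 52.0 | 0.981 |
| 0.5% | 0.98 | 0.33 | 62% | 51.7 | 0.981 |
| 1% | 1.95 | 0.65 | 86% | 51.5 | 0.980 |
| 2% | 3.90 | 1.30 | 98% | 51.0 | 0.979 |
| 5% | 9.75 | 3.25 | over 99.9% | 49.4 | 0.976 |

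If these pupils fall within the allowance of 13 per arm, evaluable n stays at 52 and power does not change. The ITT set stays at 195 in every case. The starting value of 0.981 differs from the 0.9 stated in 2.3. That is a separate matter, and only the change down the column counts here.

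**The case against.** The strongest reply is that the harm needs allocation to come before detection, and the text does not establish that order. Section 2.10 gives no time point for the professional assessment, the abstract places baseline BDI and CDI before random assignment, and the flow diagram and schedule are not shown. If the assessment precedes the envelope, these pupils may be caught in time. This stands as a limit on how often the problem occurs. It does not close the gap, because before treatment is not the same as before allocation, and none of these assessments is made a condition of entry.

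Exclusion 2 may also remove much of the group, since the Introduction notes that insomnia symptoms belong to the diagnostic criteria for depression. That also stands, and is why the group is described as residual. Its size cannot be checked.

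The chance of at least one such pupil is high at n = 195 for almost any nonzero rate, so it says little about importance. Nor is loss from the per-protocol set certain: 2.9.3 defines the set by strict adherence, mentions multiple imputation, and does not say how a pupil stopped under the protocol's own rule is classified.

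A reader might infer more than the text supports:
- **Severely depressed pupils would go untreated.** The evaluation before treatment, 2.7.1 and the stop rule itself all point to care being given.
- **One case would halt the whole study.** The sentence literally says so, but 2.2.4 points to the individual.
- **Baseline BDI of 20 or more meets the stop rule.** Section 2.8.1 uses that cut-off for the presence of depressive symptoms, not for severe depression.
- **The comparison would be biased or underpowered.** A condition present before allocation is balanced across arms in expectation, and Step 4 shows negligible power loss.

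**Conclusion.** The mismatch holds on the text. The listed criteria exclude severe depression only when it is medicated or judged to cause the sleep disorder, while 2.10 stops anyone in whom it is detected. A pupil can be eligible and meet the stop rule at the same time, and would then probably become an unreplaced dropout outside the primary analysis, though still in the ITT set.

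The practical effect is small as far as can be judged. The number affected is unknown; the range of about 1 to 10 of 195 rests wholly on the assumed rates of 0.5% to 5%. The effect on PSQI power is at most 0.005 (0.981 − 0.976) over that range. The conclusion also assumes that 2.10 refers to the individual and that allocation follows the printed criteria alone. This is a minor improvement worth making because it is cheap and concerns the allocation of minors; it does not threaten the trial's validity.

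**What to change.** 1. Add current severe depression to 2.2.2 as an exclusion in its own right, with the level set by the sponsor's clinicians. The BDI cut-off of 20 should not be borrowed for this.
2. State in 2.5 that this is judged from the baseline BDI and CDI and the professional depression assessment, all already planned, before the allocation envelope is opened.
3. Refer pupils excluded on this ground to the care that 2.10 promises.
4. Reword 2.10 so that it stops the individual's participation, and keep it for severe depression that emerges after allocation.

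The cost is one eligibility line, a sentence on timing and referral, and one change of wording. The downside is a slightly narrower population and slightly more screening. The change does not settle how the prevention question treats pupils who enter with BDI of 20 or more but are not severely depressed.
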